Prior to the development of this protocol we completed a pilot study to assess the effect of the uptake of the sit-to-stand mobility intervention by health care aides on the mobility of LTC residents with dementia. This enabled us to: (1) assess the feasibility of integrating a simple activity into the daily work of health care aides; (2) develop a method of monitoring the adherence of health care aides to the activity; (3) calculate an appropriately powered sample size; and (4) begin to assess the response of this frail LTC population to the mobility intervention [34]. In the pilot study we assessed the mobility of 32 residents at baseline and after four months of exposure to the sit-to-stand intervention with the assistance of health care aides on day and evening shifts. Residents completed a mean of 29.7 (SD = 20.79; range 2 to 76) occasions of sit-to-stand repetitions in the month prior to the measurement of their sit-to-stand performance. For every 12 occasions of repeating the sit-to-stand exercise that month, the odds of improving or maintaining performance with the 30-second sit-to-stand test doubled (p = 0.02). This early finding with a small sample provides promising evidence that exposure to the sit-to-stand functional activity carried out in the context of daily care with health care aides may delay the loss of ability to transfer in nursing home residents with dementia [45]. We hypothesize that this ability to transfer will positively influence the resident's overall mobility, function and health-related quality of life.

Our research question is: What is the effect of the sit-to-stand mobility intervention on the mobility, function, and health-related quality of life of LTC residents with dementia?

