### Sample Size

The sample size calculation for the number of resident participants is based on the primary outcome measure in the pilot study: the number of sit-to-stands that the resident is able to complete in 30 seconds. Based on our earlier pilot work, we observed residents' ability to maintain and in some instances increase the number of sit-to-stands that they could complete in 30 seconds. We judge an increase of two sit-to-stands completed in 30 seconds to be a meaningful change in the residents' mobility. Based on existing research [10,38,46,47] and the pilot study, the standard deviation of the 30-second sit-to-stand measure is 3.5 sit-to-stands. Thus we will need 49 residents in each of the intervention and the control groups to detect an increase in the number of sit-to-stands that the resident is able to complete in 30 seconds (power = 0.80; 2-tailed; α = 0.05). Assuming an attrition rate of 20% over 6 months we will recruit 60 residents to the intervention group and 60 residents to the control group. We expect to succeed in recruiting and following our sample of 120 residents based on our experience with the pilot study and the experience of [name] who recruited similar samples in two previous studies using similar recruitment methods [4,48].

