### Data Analysis

All data will be entered into an SPSS 19 database (IBM, 2010, ^©^IBM Corporation). Ten percent of the data will be double entered to assess the accuracy of data entry. We will compare the baseline characteristics of the LTC facilities, health care aides, and residents in the intervention group with the control group by computing descriptive statistics. Data are structured for each outcome measure (the 30-second sit-to-stand test; the *Functional Independence Measure*; the *Health Utilities Index Mark 2 and 3; *and, the *Quality of Life - Alzheimer's Disease*) to allow a mixed between-within subjects analysis of covariance. Specifically, the between subjects factor consists of the two groups (Control versus Intervention Group) and the within subject factor consists of the repeated measures. The covariates will include baseline characteristics the residents, including age, sex, level of cognitive impairment (Cognitive Performance Scale), extent of depression (MDS Depression Rating Scale), and extent of health instability (CHESS), and characteristics of the LTC facilities including facility size, unit size, ownership model, and quality of the environment (PEAP and ACT). A Multivariate Analysis of Covariance (MANCOVA) will be used to control the experiment-wise error rate for comparisons. Data will be analyzed according to the intention-to-treat principle, i.e. residents who relocate to another setting or who die before completing the six months of follow-up will be included in the data analysis. The extent to which the residents in the intervention facilities actually received the mobility interventions will be assessed using the documentation flowsheet measures to establish a graphical analysis of the covariate-corrected time course of performance on the mobility intervention. These analyses will be conducted using SPSS 19 in consultation with a statistician from the Centre of Health Promotion Studies at the University of Alberta.

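### MANCOVA is credited with controlling the experiment-wise error rate, but it does so only if no outcome responds; claims on function and quality of life are exposed

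*Protocol article*

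**What the plan says.** The Data Analysis section of the protocol article sets up one analysis per outcome: "Data are structured for each outcome measure", naming the 30-second sit-to-stand test, the FIM, the HUI2/3 and the QOL-AD, "to allow a mixed between-within subjects analysis of covariance". It then gives its only statement on multiplicity: "A Multivariate Analysis of Covariance (MANCOVA) will be used to control the experiment-wise error rate for comparisons". It states no adjusted significance level, step-down procedure or order of testing.

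The research question at the end of the Background spans three domains without ranking them: "What is the effect of the sit-to-stand mobility intervention on the mobility, function, and health-related quality of life of LTC residents with dementia". The Sample Size section rests on the 30-second test alone, with "power = 0.80; 2-tailed; α = 0.05", but it calls that test primary only for the earlier study: the calculation "is based on the primary outcome measure in the pilot study". So the article does not say that conclusions on function and quality of life rank below the conclusion on mobility.

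**The concern.** The sentence credits the MANCOVA with a property it does not have. An omnibus multivariate test limits false claims on individual outcomes to 5% when every outcome is unaffected. Once one outcome truly responds, the omnibus test tends to be significant for that reason, and the tests on the unaffected outcomes then run with little or no protection.

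The 30-second test measures the very action that residents practise, and the trial is sized to detect a change in it. It is therefore the outcome most likely to make the omnibus test significant. A reader of the results would take a significant FIM, HUI or QOL-AD comparison as protected at 5% across the experiment, when it may not be.

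**Working it through.** **Inputs.** From the Sample Size section: difference 2 sit-to-stands, SD 3.5, 49 per group, two-sided 0.05, power 0.80. From the Data Analysis section: four listed measures, or five scores if HUI2 and HUI3 are analysed separately. Assumed, because the article gives no value: equal correlation between outcomes of 0 to 0.7, and unadjusted 0.05 for each outcome after a significant MANCOVA.

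**1. The plan's own figure.** n per group = 2(1.960 + 0.842)² × (3.5/2)² = 2 × 7.85 × 3.0625 = 48.1, so 49. The t-test version gives 49.05. The stated 49 reproduces and is not in dispute. The standardised effect is 2/3.5 = 0.571.

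**2. Ceiling without any protection.** With m unaffected, independent outcomes each tested at 0.05, the chance of at least one false claim is 1 − 0.95^m. If only the 30-second test responds:
- four measures, m = 3: 1 − 0.95³ = 0.143
- five scores, m = 4: 1 − 0.95⁴ = 0.185

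**3. With the multivariate test first.** Simulation, 20,000 runs per setting, 49 per group, normal outcomes: Hotelling's T² (the two-group multivariate test) at 0.05 and, if significant, a t-test at 0.05 on each outcome. Ranges are over correlations 0, 0.3, 0.5 and 0.7.

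| Outcomes | True effect | Multivariate test significant | False claim on an unaffected outcome | Same, Holm across all outcomes |
|---|---|---|---|---|
| 4 | none | 0.049–0.053 | 0.032–0.051 | 0.036–0.050 |
| 4 | 30-second test, 0.571 SD | 0.589–0.960 | 0.115–0.127 | 0.038–0.044 |
| 4 | 30-second test, 1 SD | 0.984–1.000 | 0.110–0.140 | 0.039–0.049 |
| 5 | none | 0.049–0.050 | 0.032–0.048 | 0.034–0.048 |
| 5 | 30-second test, 0.571 SD | 0.531–0.957 | 0.133–0.149 | 0.033–0.045 |
| 5 | 30-second test, 1 SD | 0.975–1.000 | 0.130–0.184 | 0.035–0.048 |

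The MANCOVA does its job in the rows with no effect. In the 1 SD rows the error equals that of unprotected testing to within 0.001.

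**4. When more than one outcome responds.** Four measures, same procedure, 6,000 runs per setting:
- a second outcome also affected (0.3 or 0.57 SD): 0.08 to 0.10; the ceiling for two unaffected outcomes is 1 − 0.95² = 0.0975
- three of four affected: 0.045 to 0.053; one unaffected outcome at 0.05 cannot exceed 0.05 beyond simulation error

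**5. Power for the 30-second test under the alternatives.** Five scores, only this test affected by 0.571 SD, 8,000 runs per setting:
- tested alone at 0.05: 0.80
- behind the MANCOVA: 0.52, 0.61 and 0.70 at correlations 0, 0.3 and 0.5
- Holm across five scores: 0.58

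As a rough check on the last figure, Holm's first step uses 0.05/5 = 0.01. The expected test statistic is 0.571 × √(49/2) = 2.83, and the normal approximation gives Φ(2.83 − 2.58) ≈ 0.60.

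**The case against.** Four points can be made for the plan.

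- **The faulty step is inferred.** The article does not say that individual outcomes are tested at unadjusted 0.05 after the MANCOVA, and a fuller analysis plan might add an adjustment. This stands as a limit: unadjusted 0.05 is the plain reading, not a stated fact. It does not remove the point, because the sentence credits the MANCOVA itself with the control.
- **The single-responder scenario is not the one hoped for.** A reader might infer that, if the trial succeeds, false claims run at about three times the nominal rate. The documents do not support that. The Background hypothesises that better transfers will carry over to overall mobility, function and quality of life. The FIM contains transfer and locomotion items, and the HUI2 and HUI3 have mobility and ambulation attributes. If three of four outcomes respond there is no inflation. Three times also needs five scores, whereas the Abstract numbers four outcome measures. This objection stands in full.
- **The 30-second test is not at risk.** A reader might infer that the main mobility result is compromised. Where that test truly responds, its rejection cannot be a false positive. This also stands.
- **The simulation is simplified.** It treats residents as independent and leaves out covariates, repeated measures and the six facilities. The figures isolate the multiplicity question and are not error rates for this trial as it will be run.

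**Conclusion.** The point holds in a limited form. The MANCOVA controls the experiment-wise error rate when no outcome is affected. It does not do so when at least one outcome responds and two or more do not, and no other control is named. Under the plan's own effect on the 30-second test alone, the chance of a false claim elsewhere is about 0.11 to 0.13 with four measures (0.115/0.05 = 2.3 to 0.127/0.05 = 2.5 times nominal), or about 0.13 to 0.15 with five scores. It is about 0.09 with two of four responding and about 0.05 with three.

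The size depends on the assumed correlations, on unadjusted 0.05 after the MANCOVA, and on independent residents. That inflation occurs with two or more unaffected outcomes does not depend on the particular correlation within the range examined. The exposure is confined to claims on function and quality of life. Severity is moderate.

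**What to change.** Replace the sentence on MANCOVA in the Data Analysis section with wording to this effect:

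- The MANCOVA, if kept, is a global test of any difference between the groups and does not support claims on individual outcomes.
- The 30-second sit-to-stand test, on which the sample size rests, is tested first at two-sided 0.05.
- Only if it is significant are the FIM, HUI2, HUI3 and QOL-AD tested, with Holm-adjusted p-values at 0.05.

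This holds the joint error at 5% whichever outcomes respond. If the 30-second test is unaffected, any false claim first requires that test to be significant, which has probability at most 0.05. If it is affected, Holm limits false claims among the other four scores to 0.05.

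No new data are needed. The 30-second test keeps its planned power of 0.80 under the plan's own assumptions. The cost falls on the other outcomes: a stricter threshold for each (0.05/4 = 0.0125 at Holm's first step), and no claim on any of them if the 30-second test fails. Holm across all five scores would also control the error and would allow such claims, but it would cut power for the 30-second test to about 0.58.

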### Intervention group

Residents in the three intervention facilities will be exposed daily to the intervention for 6 months. This will enable an assessment of the effect of the intervention on residents' mobility over time and a preliminary assessment of the sustainability of the intervention. Their mobility, function in basic activities of daily living, and health-related quality of life will be measured at baseline, 3 months and 6 months.

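### The repeated-measures ANCOVA and MANCOVA, as named and with no further step stated, drop residents without a 3- or 6-month value, although the plan says those who die or relocate will be included

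*Protocol article*

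**What the plan says.** Outcomes "will be measured at baseline, 3 months and 6 months" (Protocol article, Intervention group); the Control group section sets the same three occasions for control residents.

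Data Analysis says that the data for each outcome are structured "to allow a mixed between-within subjects analysis of covariance". The between-subjects factor is control versus intervention, and "the within subject factor consists of the repeated measures". It adds: "A Multivariate Analysis of Covariance (MANCOVA) will be used to control the experiment-wise error rate for comparisons". The software is named as well: "These analyses will be conducted using SPSS 19".

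The same section commits to intention-to-treat and explains the term: "residents who relocate to another setting or who die before completing the six months of follow-up will be included in the data analysis".

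The Sample Size section expects loss: "Assuming an attrition rate of 20% over 6 months", 60 residents per group are recruited so that roughly the required 49 remain. The article names no imputation, no likelihood-based model and no rule for outcomes after death.

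**The concern.** The word mixed in the article's description refers to mixing between- and within-subject factors. It does not denote a mixed-effects model. The classical form of that analysis needs a complete set of repeated values from each resident, and a joint MANCOVA also needs every outcome in the set. A resident who dies in month 4 has no 6-month value and is deleted. One paragraph therefore names methods that omit a group of residents and says that the same group will be included. Followed as written, it yields a completers' analysis under an intention-to-treat label.

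This matters because loss is unlikely to be unrelated to outcome. The Schedule of Intervention section itself ties expected attrition to the frailty of the population. The Adverse Events section describes a case-by-case decision on staying in the study after a fall and mentions it only for intervention facilities, so missing data could arise differently by arm. Allocation is not randomised, and the outcome assessor cannot be kept blind. If one arm loses more failing residents than the other, a completers' comparison flatters that arm.

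**Working it through.** **1. The plan's own figure.** Inputs from Sample Size: difference 2 ("We judge an increase of two sit-to-stands completed in 30 seconds to be a meaningful change in the residents' mobility"), SD 3.5, two-sided α 0.05, power 0.80.

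n per group = 2 × [3.5 × (1.960 + 0.842) / 2]² = 48.07, rounded up to 49. The stated 49 reproduces; the t-based solution is 49.05. For 20% attrition, 49 / 0.80 gives 62 and 49 × 1.2 gives 59. The stated 60 lies within two of either, so no stated figure is wrong.

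**2. Who leaves the analysis.**

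| Resident | Repeated-measures ANCOVA of the 30-second test, standard form |
|---|---|
| Dies before 6 months | Dropped: no 6-month value can exist |
| Relocates, assessed at 3 and 6 months | Kept |
| Relocates, misses either assessment | Dropped |
| Has the 30-second test at every visit, lacks a proxy questionnaire | Kept here; dropped from that questionnaire's ANCOVA and from a joint MANCOVA |

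**3. How many.** 60 × 0.80 = 48 per group, so 96 are analysed and 120 − 96 = 24 are lost, if all the planned attrition means a missing visit. Residents who stay in the study but miss one visit would add to this; the article gives no figure for them.

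**4. Power.** On the plan's own basis (independent residents, single comparison), power = Φ(2 / [3.5 × √(2/n)] − 1.960).

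- n = 60: Φ(3.130 − 1.960) = 0.879 (t-based 0.874)
- n = 48: Φ(2.799 − 1.960) = 0.799 (t-based 0.791)

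Other attrition rates, as assumptions:

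| Attrition | Residents lost | Power |
|---|---|---|
| 10% | 12 | 0.844 |
| 30% | 36 | 0.745 |
| 40% | 48 | 0.679 |

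At the planned 20% the trial keeps essentially its design power.

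**5. Possible bias.** Let f be the share dropped in an arm and D the completer mean minus the dropout mean. The arm's full mean is (1 − f) × C + f × (C − D) = C − f × D, so the completer mean C is too high by f × D. With the same D in both arms, the bias in the group difference is (f₁ − f₂) × D. The article gives neither f by arm nor D, so these are assumed ranges:

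| Dropout difference | D = 1 | D = 4 |
|---|---|---|
| 0 | 0 | 0 |
| 5 percentage points | 0.05 | 0.20 |
| 20 percentage points | 0.20 | 0.80 |

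Against the target of 2, 0.05 / 2 = 2.5% and 0.80 / 2 = 40%. D must be read on the scale that the analysis compares, after baseline and covariates are taken into account, which may make it smaller than the raw gap. If D differs between arms, equal dropout no longer guarantees zero bias.

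**The case against.** The strongest reply is that the article never says complete cases, that missing-data handling commonly sits in a full protocol or analysis plan not shown here, and that the intention-to-treat sentence can be read as a promise that some such step will exist. Imputing before the ANCOVA and MANCOVA would let both statements stand. This is right to the extent that a missing imputation section is no finding, and it would be too strong to say that the two statements cannot both be carried out. But the article fixes both the method and the rule, and an unseen document could reconcile them only by adding to or changing the stated method.

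A reader might also infer more than the text supports:

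- **That all relocated residents are dropped.** Nothing says they will not be followed; one who is still assessed stays in.
- **That the attrition allowance contradicts intention-to-treat.** Recruiting extra residents to allow for lost data is routine and compatible with it, and the figures reproduce.
- **That one missing questionnaire removes a resident from the 30-second test analysis.** The ANCOVA is set up separately for each outcome; only a joint MANCOVA has that effect.
- **That the trial loses its power.** At 20% attrition it does not.
- **That the result will be biased by a known amount or in a known direction.** The dropout mechanism is not given, and a dropout's mean outcome is not even defined at visits after death.

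**Conclusion.** The concern holds in this limited form: as written, the named analyses do not deliver the stated inclusion of residents who die, nor of relocated residents who go unassessed. The loss is up to about 24 of 120 residents, taking the plan's 20% attrition as missing visits. The consequences are possible selection bias and a label that does not describe the analysis.

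The bias range of about 0.05 to 0.8 sit-to-stands rests on assumed dropout differences and gaps and on an equal gap in the two arms; it is an illustration, not a prediction. Listwise deletion is inferred from the standard form of the named methods. The point should be settled before analysis because it decides who counts in the comparison for every outcome.

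**What to change.** Replace the repeated-measures ANCOVA with a likelihood-based linear mixed model for each outcome, with group, visit, their interaction and the planned covariates. Enter the baseline, 3-month and 6-month values all as responses, so that every enrolled resident with a baseline value is kept, including those who die before month 3. Multiple imputation before the named analyses is an acceptable alternative.

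Death needs its own statement, because either method otherwise implicitly supplies outcomes beyond it. State that the estimate refers to residents while alive, and add a sensitivity analysis that ranks death as the worst outcome.

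If the named methods are kept without any such step, describe the analysis as complete-case and withdraw the statement that residents who die or relocate are included.

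The cost is revised wording and modest extra programming, and the software already named can be used. The price in assumptions is missing at random: given the observed values, loss must not depend on the unseen ones. Residents with only a baseline value will add little information about the group difference even so. The modelling change needs no new data; following relocated residents to their new setting is a separate, optional step with its own field cost.

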### Ethical Considerations

We have received ethical approval for the study from the Health Research Ethics Board of the University of Alberta. We also have received a letter of support from the senior administrator of each of the six participating LTC facilities.

#### Adverse Events

Monitoring of adverse events in the intervention facilities will be compared with adverse events in the control facilities. We expect to see a reduced incidence of resident falls and related injuries in the intervention facilities. Likewise we expect to see a reduction in the injury of health care aides working in the intervention facilities. Resident safety is unlikely to be compromised given our pilot study experience and the experience of others in carrying out exercise interventions in a similar population [20,28,37,42,104,105]. Although the mobility intervention is expected to reduce residents' risk of falls by maintaining or improving their mobility, maintaining mobility extends the time that residents are at risk of a fall. We will monitor resident participants' falls monthly and compare these with their baseline pattern of falls three months prior to entering the study. In the event of a resident participant falling in one of the intervention facilities the principal investigator will decide in collaboration with the LTC facility manager whether or not that resident should remain in the study.

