## Background

Immobility is a major factor contributing to a reduced quality of life and preventable adverse events among older adults living in residential long-term care (LTC). Of the more than 150,000 older Canadians living in LTC facilities [1] almost 90% have some type of reduced mobility, [2] with approximately 40% of LTC residents with dementia losing their ability to walk annually [3,4]. Immobility leads to a loss of ability in activities of daily living (e.g. dressing or toileting), increased risk of falls and medical problems such as pressure ulcers and incontinence [5-9]. Although the adverse consequences of immobility and bed rest have been known for many years, elderly residents living in LTC facilities still commonly sit in wheelchairs or lie in bed for prolonged periods of time, in many cases for most of their waking hours [10,11].

When a resident loses the ability to stand up from a chair, the bed, or a toilet, both the time and the cost of health care escalate dramatically [12,13]. Transferring the resident then involves seeking a second health care aide to assist and often retrieving a mechanical lift to assist with the transfer. In the resource constrained environment of LTC, the extra time required for a transfer may translate to fewer transfers, significant delays in toileting (if toileted at all), and higher risk for a host of adverse consequences associated with immobility. Inactivity significantly affects quality of life for LTC residents in terms of ability to walk, balance and transfer [14-16].

Residents' immobility has ramifications on the nature of the work in LTC. Increased resident dependency increases the workload for health care aides as they perform more lifting and thereby heightens their risk of injury [17,18]. Approximately 60% of the loss of ability to walk in residents with dementia is potentially treatable [4]. The effectiveness of rehabilitation to facilitate mobility has been studied in LTC settings with dedicated research assistants or extensively trained staff caregivers [19-30]; however, the evidence that such rehabilitative approaches will be transferred, accepted, or sustained in the typically resource constrained environments of contemporary residential LTC facilities is lacking [31-33]. Few investigators have examined the effectiveness of techniques to encourage mobility by the usual caregivers in these settings, that is, by the unregulated health care aide workforce.

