### Control group

Resident participants in the control facilities will receive usual care. The only change in their routine will be the measurement of mobility, function and health-related quality of life on three occasions as for residents in the intervention group. Health care aides may work in more than one unit in a facility thus intervention and control groups will be designated at the facility level rather than the unit level to avoid contamination of the control group. It is also possible that some health care aides may work in more than one facility. We will assess the extent of contamination of the control group at the end of the study by asking health care aides who work control facilities if they have ever encouraged residents in the control facilities to repeat sit-to-stands.

LTC facilities in the intervention group will be matched to the control group facilities on ownership model (public, private for-profit, voluntary not-for-profit) and size because quality of care and resident outcomes are associated with ownership models [49-54] and size [48,49,52]. To assess the comparability of the intervention and control facilities a research assistant will gather information about each facility by: a) interviewing managers to obtain information such as staff-to-resident ratios on each shift, availability of rehabilitation services and size of units; b) observing activity across both the day and evening shifts using a structured observation schedule; and c) measuring environments using two standardized instruments: the Alberta Context Tool and the Professional Environmental Assessment Protocol (PEAP). Drawing on data collected from the observations and data elicited during the manager interviews, total PEAP scores will be calculated immediately following each manager interview.

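### Falls are to be compared between facilities and with each resident's own pre-entry pattern, but neither comparison is stated to use the other, and no time-at-risk denominator is named

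*Protocol article*

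**What the plan says.** The Adverse Events section (under Ethical Considerations) begins with a concurrent comparison: "Monitoring of adverse events in the intervention facilities will be compared with adverse events in the control facilities". It then gives the direction the investigators expect: "We expect to see a reduced incidence of resident falls and related injuries in the intervention facilities". It recognises a complication, that "maintaining mobility extends the time that residents are at risk of a fall". It then adds a second comparison: "We will monitor resident participants' falls monthly and compare these with their baseline pattern of falls three months prior to entering the study".

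Three other places bear on how these are read:

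- The Control group section applies the same term to controls: "Resident participants in the control facilities will receive usual care". The before/after sentence therefore covers both groups.
- The same section says that intervention and control facilities are matched on ownership model and size. Methods/Design calls the study quasi-experimental, with three facilities in each group.
- Data Analysis describes a between-within analysis of covariance for four outcome measures: the 30-second sit-to-stand test, the FIM, the HUI2/3 and the QOL-AD. Falls are not among them.

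**The concern.** Each comparison, as stated, leaves out what the other would supply.

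The facility comparison has a concurrent control but no stated use of the fall level before entry. With six facilities allocated without randomisation, and matching that does not involve falls, the two groups may start at different fall rates. A follow-up-only comparison passes that difference straight into the result.

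The before/after comparison uses the baseline but is not stated as a contrast between groups. Change should be expected in this population whatever the intervention does. The Background reports "approximately 40% of LTC residents with dementia losing their ability to walk annually", and the Sample Size section plans for residents leaving: "Assuming an attrition rate of 20% over 6 months". Everyone in the look-back was also alive and still able to transfer at its end, because that is how residents become eligible.

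The denominator is a further gap. The look-back is three months and follow-up lasts six ("Residents in the three intervention facilities will be exposed daily to the intervention for 6 months"), some residents will leave, and some may have been admitted less than three months before entry. A comparison of falls needs a statement of the time they are counted over.

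Falls are the resident risk that the section discusses most directly. A conclusion in either direction, fewer falls or more, could come from starting differences or background change rather than from the intervention.

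**Working it through.** **Is there a figure to reproduce?** None for falls. The article gives no fall rate in either group, before or after entry. Its one computed figure, 49 residents per group, concerns the sit-to-stand test: 2 × (1.96 + 0.84)² × 3.5² / 2² ≈ 48, or 49 with the small-sample allowance. It reproduces but says nothing about falls.

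**Set-up.** Define four quantities, all assumed because the article gives none:

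- *b* = pre-entry fall rate per resident-month in the control group
- *s* = ratio of pre-entry rates, intervention to control
- *t* = background change from pre-entry to follow-up, taken as the same in both groups
- *r* = true effect of the intervention on the fall rate

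The follow-up rates are *b·t* in controls and *b·s·t·r* in the intervention group. Hence:

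- facility comparison at follow-up: (*b·s·t·r*) / (*b·t*) = *s·r*
- before/after in the intervention group: (*b·s·t·r*) / (*b·s*) = *t·r*
- before/after in the control group: (*b·t*) / *b* = *t*
- relative change: (*t·r*) / *t* = *r*

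**Illustrative values.**

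| True effect *r* | Background *t* | Starting ratio *s* | Facility comparison *s·r* | Before/after, intervention *t·r* | Relative change |
|---|---|---|---|---|---|
| 1.3 | 0.75 | 1.0 | 1.3 | 0.975 | 1.3 |
| 1.3 | 1.3 | 1.0 | 1.3 | 1.69 | 1.3 |
| 1.0 | 1.3 | 1.0 | 1.0 | 1.3 | 1.0 |
| 1.3 | 1.0 | 0.75 | 0.975 | 1.3 | 1.3 |
| 1.0 | 1.0 | 1.3 | 1.3 | 1.0 | 1.0 |

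Rows 1 to 3 show the before/after comparison hiding, exaggerating or inventing an increase. Rows 4 and 5 show the facility comparison hiding or inventing one when the groups start at different rates. The relative change returns the true value in every row, provided that the background change is common to both groups.

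**Denominator.** Suppose 60 residents per group and 20% attrition spread evenly over six months (the even spread is an assumption). Average time lost is 10%, so 60 × 6 = 360 resident-months become 324. With an unchanged fall rate per resident-month, falls per enrolled resident per month would be 324/360 = 0.90 of the pre-entry level. Falls per resident-month actually spent in the facility would be 1.00 of it. The article does not say which is meant.

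**The case against.** The strongest reply is that the article already plans a concurrent comparison and places falls within it. The before/after sentence is an addition, it is worded to cover controls, and nothing says that the control group's change will be ignored. All of this stands. A reader who sees only the before/after sentence might infer that falls have no control comparison; the opening of the same section shows otherwise.

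A reader might also infer that the investigators intend to treat fewer falls than before entry, in the intervention group alone, as evidence of safety. The article does not say so. The expected reduction follows the between-facility sentence. The before/after sentence stands just ahead of the provision on whether a resident who falls stays in the study, so it may be meant partly as individual monitoring.

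Unequal windows are not an error in themselves: monthly counts can be turned into monthly rates, and nothing says that raw totals will be compared.

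It is tempting to size the bias from the annual loss of walking and the assumed attrition. That would require assuming that residents who stop walking fall less, whereas the Background lists falls among the consequences of immobility. It would also need a denominator that the article does not specify. No such figure is offered here.

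Finally, a condensed article may leave model detail to the full protocol, which could already contain the contrast. That limits the weight of the point but does not remove it: the article does name the comparators for falls, and each of those, taken as stated, is open to bias.

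**Conclusion.** The point holds in a limited form. The plan has both a control group and a baseline for falls, but states them as two separate comparisons. One is exposed to starting differences between non-randomised facilities, the other to background change, and neither has a stated denominator. Neither the size nor the net direction of the bias can be given, since no fall rate appears anywhere; the tabulated ratios show only how it arises.

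This is an inexpensive improvement to a safety comparison. It does not show that the planned data are inadequate. The better contrast itself assumes that background change would have been similar in the two groups, which three facilities per group cannot guarantee.

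**What to change.** In the Adverse Events section, state that:

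- falls of resident participants will be expressed per resident-month lived in the facility, taken from the same record source in both groups and in both periods;
- the main fall comparison is the change from the three-month pre-entry rate to the follow-up rate in the intervention group, relative to the same change in the control group (or, equally acceptable, the between-group follow-up rate adjusted for the pre-entry rate);
- before/after figures for one group alone are descriptive.

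Counting resident-months puts the two periods and the two groups on the same footing for time observed. It does not remove falls that arise because residents stay mobile for longer; these remain part of the intervention's overall effect and should be described as such.

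The cost is a few sentences and a little more analysis, because pre-entry and monthly falls are already planned for both groups. The relative change will have a wider interval than a one-group before/after comparison, by an amount that cannot be given without a fall rate. Recently admitted residents will contribute less baseline time.
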